### Study end points

Primary endpoint is the occurrence of HAP within 28 days of randomization. Pneumonia is considered when at least 2 signs (body temperature > 38°C; leukocytosis >12 000/mL, or leukopenia <4000/mL; purulent pulmonary secretions) associated with the appearance of a new infiltrate are present or when changes occur in an existing infiltrate on chest x-ray. The diagnosis needs to be confirmed by a respiratory tract sample using a quantitative culture with a predefined positive threshold of 10^4 ^colony-forming units per milliliter (CFU/mL) for a bronchoalveolar lavage or non bronchoscopic sample, of 10^3 ^CFU/mL for a protected specimen brush and of 10^6 ^CFU/mL for a tracheal sample. Hospital-acquired pneumonia is defined as pneumonia that occurs 48 hours after admission that had not been incubating at the time of admission.

The secondary outcomes are duration of mechanical ventilation and length of ICU stay, antibiotic free days, rate of death, other infections, organ failures, and duration of vasopressor support on day 28 and in ICU. Safety is assessed by recording adverse events.

An ancillary study will assess the mortality, the long term neurological and psychological recovery on the -6^th ^and -12^th ^month.

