### Follow up

The following variables are collected: demographics, Apache 2, MGAP score [15], injury severity score and abbreviated injury score, fluid infusions, vasopressors, antibiotherapy, etomidate use, surgery, intracranial pressure, infections, organ failures, natremia, length of ventilatory support, and ICU hospitalisation and death in ICU and at day 28 are recorded. In ICU, clinical assessments are performed at least twice a day. Clinical evaluation for diagnosis of pneumonia are performed twice a day in the ICU. A chest x-ray is performed as soon as pneumonia is suspected after clinical examination. A respiratory tract sample is collected for bacteriological analysis before any modification of antibiotic therapy. Patients or relatives are contacted on -6 and -12 month for evaluation of neurological recovery (GOS, Kartz index), of quality of life, of depression disorder (HAD scale, SF-36 and I.E S-R scores) and of mortality.

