## Discussion

The Corti-TC trial is the second randomized controlled study powered to investigate prolonged low dose of corticosteroid therapy in severe trauma patients, and the first one focusing on severe TBI patients.

Cortisol production is necessary for normal host defence against infection. Hydrocortisone dampens inflammation while preserving innate immunity [17] and improves the recovery from severe community-acquired pneumonia [18]. Trauma-induced inflammation, which is exacerbated in cases of corticosteroid insufficiency [19], leads to infection [12]. In the HYPOLYTE study [10], low dose of hydrocortisone decreased rate of HAP in intubated trauma patients with corticosteroid insufficiency.

The primary outcome of this trial is HAP, that could be considered as a shortcoming since the prevention of HAP does not always improves outcomes of ICU patients [20]. Infections are the most frequent cause of complications in severely injured patients [21]. The incidence of pneumonia is particularly high in trauma patients, reaching up to 50% [2-4]. Post-trauma pneumonia is responsible for an increased morbidity (duration of mechanical ventilation and ICU hospitalization) [5,6], and the average cost for each pneumonia episode is high [8]. In the HYPOLYTE study, together with a decreased in rate of HAP, hydrocortisone decreased both duration of mechanical ventilation and ICU length of stay. Thus, we considered that the most relevant endpoint would be HAP.

Criteria for HAP diagnosis has not been studied in trauma patients treated with hydrocortisone and theoretically the study treatment may decrease the ability of clinician's to diagnose HAP. For community-acquired pneumonia, the body temperature of patients treated with a high dose of glucocorticoid was slightly decreased (by less than 0.5°C) as compared to placebo-treated patients [22], but to our knowledge, the effects of stress dose hydrocortisone (if any) are unknown in trauma patients. Also, in case of CIRCI hydrocortisone should restore the ability to develop fever, and patients without CIRCI (left untreated) should not present any dysregulation in thermoregulation abilities. Finally, we assumed that hydrocortisone with fludrocortisone will not biased HAP diagnosis.

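### The primary endpoint definition prints white-cell limits per mL (1000-fold too low) and leaves unclear whether a changed infiltrate needs clinical signs; possible steroid effects on the signs are settled by assumption

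*Protocol article*

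**What the plan says.** The primary endpoint is hospital-acquired pneumonia (HAP) within 28 days of randomization. The Study end points section builds it in three layers.

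- **Signs.** The rule opens "Pneumonia is considered when at least 2 signs (body temperature > 38°C" and continues with "leukocytosis >12 000/mL, or leukopenia <4000/mL; purulent pulmonary secretions". That is two of three: temperature, white cells, secretions.
- **Imaging.** The signs must be "associated with the appearance of a new infiltrate are present or when changes occur in an existing infiltrate on chest x-ray".
- **Culture.** "The diagnosis needs to be confirmed by a respiratory tract sample using a quantitative culture with a predefined positive threshold", with a threshold set for each sampling method.

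The Follow up section adds that "A chest x-ray is performed as soon as pneumonia is suspected after clinical examination", so imaging depends on prior suspicion.

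The Discussion concedes that treatment could in theory make HAP harder to diagnose. It cites a temperature fall of under 0.5°C with high-dose glucocorticoid in community-acquired pneumonia and says that the effect of stress-dose hydrocortisone in trauma patients is unknown. It then argues that "in case of CIRCI hydrocortisone should restore the ability to develop fever" and closes with "we assumed that hydrocortisone with fludrocortisone will not biased HAP diagnosis". It does not discuss white cells.

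**The concern.** The definition fixes who counts as an event in the primary analysis, and it is faulty in two places. The white-cell limits carry a unit that makes one of the three signs meaningless. The wording on infiltrates allows two readings, so two investigators could classify the same patient differently.

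A further question concerns the comparison between arms. Temperature and white-cell count could both respond directly to a corticosteroid. If the drug changes how often the signs appear during a true pneumonia, part of an observed difference in HAP could reflect detection rather than prevention. Blinding does not stop a drug from altering a temperature or a blood count. The article names this risk and then sets it aside by assumption.

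**Working it through.** **1. Unit.** 1 mL = 1000 mm3.

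- 12 000 per mL / 1000 = 12 per mm3 (0.012 × 10^9/L).
- 4000 per mL / 1000 = 4 per mm3 (0.004 × 10^9/L).

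Blood counts normally run in the thousands per mm3. As printed, the upper limit is always exceeded and a count is never below the lower one. The white-cell sign is always positive, and two of three becomes at least one of fever and purulent secretions.

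To show the scale, take sign frequencies f (fever), w (white cells) and s (secretions), assumed independent. The values are assumptions; the article gives none.

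- Intended rule: fw + fs + ws − 2fws.
- Printed rule: 1 − (1 − f)(1 − s).

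| f / w / s | Intended | Printed |
|---|---|---|
| 0.3 / 0.3 / 0.3 | 21.6% | 51% |
| 0.5 / 0.5 / 0.4 | 45% | 70% |
| 0.6 / 0.6 / 0.5 | 60% | 80% |

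These are shares meeting the sign layer only, before imaging and culture.

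**2. Infiltrate clause.** There are two possible readings.

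- A: at least 2 signs AND (new infiltrate OR changed infiltrate), plus culture.
- B: (at least 2 signs AND new infiltrate) OR changed infiltrate, plus culture.

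The second clause has its own conjunction and verb and names no sign, so the grammar favours B. The sense may favour A. They differ for a patient with a changed infiltrate, a positive culture and fewer than two signs.

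**3. Detection by arm.** The sample size targets patients with corticosteroid insufficiency (CI), who also form the modified intention-to-treat set. If hydrocortisone restores fever in these patients, those on placebo lack that restoration, and one endpoint sign then differs between the randomised groups. Pointing to patients without CI, who are left untreated, does not address this contrast. Absence of bias therefore does not follow from the stated premises.

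**4. Possible size (assumed losses).** Inputs from the Statistical consideration section: 70% HAP on placebo, a 20-point reduction, two-sided 5%, power 90%, 121 per group, 326 in total, 75% with CI.

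The plan's figure reproduces: n = (1.960 + 1.282)² × (0.7×0.3 + 0.5×0.5) / 0.2² = 120.8, so 121 per group. With 326 randomised, 326 × 0.75 / 2 = 122.25, so about 122 per group.

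With no true effect (70% in both arms) and relative detection loss L on treatment, the observed rates are 0.70 and 0.70(1 − L). Using d = 0.70L and SE = √{[p1(1−p1) + p2(1−p2)]/122}, P(significant benefit) = Φ(d/SE − 1.96).

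| L | Observed rates | d | SE | P(false benefit) |
|---|---|---|---|---|
| 0 | 70% v 70% | 0 | 0.0587 | 2.5% |
| 5% | 70% v 66.5% | 0.035 | 0.0596 | 8.5% |
| 10% | 70% v 63% | 0.070 | 0.0603 | 21% |
| 15% | 70% v 59.5% | 0.105 | 0.0608 | 41% |

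In the opposite direction, suppose the planned effect is real and 10% of HAP is missed on placebo. Then 70% v 50% becomes 63% v 50%: d = 0.13, SE = 0.0629, Φ(2.07 − 1.96) ≈ 54% power, against about 90% without loss.

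**The case against.** **The unit is a slip.** The numerals make sense only per mm3, and a sign that every patient meets cannot be what clinicians apply. This is probably right, and a reader should not infer that cases have in fact been classified per mL: the case report form is not shown. The printed figure in the primary endpoint is still wrong.

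**An x-ray change alone is never an event.** This stands. A reader might infer from the loose clause that radiology without clinical findings suffices. Culture at threshold is required for every diagnosis, and the x-ray itself follows clinical suspicion. These safeguards limit the harm but do not settle which reading applies.

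**The two complaints about white cells cannot both bite.** This is correct. If the sign is always positive as printed, steroids cannot mask it. The detection point about white cells applies only to the sensible per-mm3 reading.

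**Steroid bias is disclosed, and the cited evidence is weak.** This largely stands. The temperature evidence comes from high doses in another disease and amounts to less than half a degree. A tempting stronger reading is that treatment will mask signs and be declared protective. The documents do not support it: restored fever would raise detection on treatment and count against a benefit.

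**The probabilities overstate the case.** The losses are invented for illustration and applied to all HAP to day 28, although study drug lasts at most 10 days. Masking one sign loses a case only if fewer than two remain. The primary analysis is an adjusted Cox model, not a comparison of proportions. All of this is fair; the figures show sensitivity, not an expected bias.

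**An extra sensitivity analysis may already exist.** The full protocol and analysis plan are not shown, so its absence from the article is not held against the trial.

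**Conclusion.** The main point holds on the text: the primary endpoint definition is wrong as written. The white-cell limits are 1000-fold too low for the evident intent, and read literally they reduce the sign rule to fever or purulent secretions. Whether a changed infiltrate needs the two signs is ambiguous. Culture and suspicion-led imaging limit the practical effect, which depends on what the case report form says.

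The secondary point is narrower. The no-bias conclusion is an assumption that the article's own fever argument does not support, and white cells are left out. The direction of any bias is unknown. The 8.5%, 21% and 41% figures rest on assumed one-sided losses of 5%, 10% and 15%, 70% true HAP in both arms and about 122 patients per group; a loss on placebo would lower power instead. The documents do not support a claim that bias is present or that it favours treatment. The planned sample size is unaffected.

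**What to change.** 1. Change the white-cell unit from mL to mm3 for both limits.
2. Reword the rule as: at least 2 signs AND (new infiltrate OR change in an existing infiltrate), confirmed by quantitative culture at the stated threshold.
3. Check, blinded to allocation, that the case report form and the cases already classified use this rule. The Trial status section reports 110 patients enrolled and a first interim analysis due in November 2011, so the check is best done before that analysis.
4. State the no-bias sentence as an untested assumption of unknown direction, and mention white cells. This improves the account but changes no result.
5. Where suspected episodes are recorded, and unless already planned, add a sensitivity analysis that defines HAP by new or changed infiltrate plus culture at threshold, ignoring temperature and white cells.

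Items 1, 2 and 4 cost only text, and item 3 a short blinded review. Item 5 is one extra analysis if the data exist; the article lists infections among the collected variables but does not say that unconfirmed suspected episodes are kept. It cannot recover episodes never suspected, because imaging follows suspicion.

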### Follow up

The following variables are collected: demographics, Apache 2, MGAP score [15], injury severity score and abbreviated injury score, fluid infusions, vasopressors, antibiotherapy, etomidate use, surgery, intracranial pressure, infections, organ failures, natremia, length of ventilatory support, and ICU hospitalisation and death in ICU and at day 28 are recorded. In ICU, clinical assessments are performed at least twice a day. Clinical evaluation for diagnosis of pneumonia are performed twice a day in the ICU. A chest x-ray is performed as soon as pneumonia is suspected after clinical examination. A respiratory tract sample is collected for bacteriological analysis before any modification of antibiotic therapy. Patients or relatives are contacted on -6 and -12 month for evaluation of neurological recovery (GOS, Kartz index), of quality of life, of depression disorder (HAD scale, SF-36 and I.E S-R scores) and of mortality.

### Statistical consideration

The required sample size is calculated from results of the HYPOLYTE study [10]. The power calculation is performed for comparison between the hydrocortisone and placebo groups in patients with corticosteroid insufficiency. The sample size needed to detect an absolute decrease in pneumonia incidence of 20% is 121 patients in each group, assuming a rate of 70% in the placebo group, in a 2-sided test performed with a statistical power of 90% and an α risk of 5%. Assuming a rate of 75% of corticosteroid insufficiency [10], 326 patients (approximately 163 patients in each group, and 41 patients with normal corticosteroid function who are untreated) are needed. Two a priori interim analyses using the O'Brien and Fleming method for α risk spending are planned respectively after the inclusion of 110 and 220 patients.

An ITT and a mITT analysis will be performed. Because the patients with adapted corticosteroid function are left untreated (when the cosyntropin test show no corticosteroid insufficiency), a modified intention-to-treat (mITT) analysis that includes only the patients with corticosteroid insufficiency is planned.

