**Methods:**

The CORTI-TC (Corticotherapy in traumatic brain-injured patients) trial is a multicenter, randomized, placebo controlled, double-blind, two-arms study. Three hundred and seventy six patients hospitalized in Intensive Care Unit with a severe traumatic brain injury (Glasgow Coma Scale ≤ 8) are randomized in the first 24 hours following trauma to hydrocortisone (200 mg.day^-1 ^for 7 days, 100 mg on days 8-9 and 50 mg on day-10) with fludrocortisone (50 μg for 10 days) or double placebo. The treatment is stopped if patients have an appropriate adrenal response. The primary endpoint is HAP on day-28. The endpoint of the ancillary study is the neurological status on 6 and 12 months.

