### Randomization

Patients eligible for inclusion should be randomized, and the study treatment is started within the first 24 hours. Patients are randomized in a 1:1 ratio in fixed blocks of 12 and stratified according to the center and MGAP score [15] by a computerized number generator list provided by a statistician not involved in the determination of eligibility or in the assessment of outcomes. All assignments are made through a dedicated, pass-word protected, SSL-encrypted website. Randomized patients are given a number corresponding to a «Corti-TC treatment pack» that contains: 20 × 100 mg vial of hydrocortisone or placebo, 10 pills of 50 μg of fludrocortisone or placebo and a sheet for schedule administration.

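### The abstract gives 376 patients and the sample-size section 326; the stated inputs support 326, and one maximum should be fixed before the first interim result is seen

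*Protocol article*

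**What the plan says.** The Methods paragraph of the abstract gives the number randomised: "Three hundred and seventy six patients hospitalized in Intensive Care Unit with a severe traumatic brain injury".

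The section Statistical consideration builds the number from its parts. The power calculation concerns patients with corticosteroid insufficiency. Its control rate is set by "assuming a rate of 70% in the placebo group", and it takes 90% power and a two-sided 5% level. On that basis the requirement for an "absolute decrease in pneumonia incidence of 20% is 121 patients in each group". The section then concludes that "326 patients (approximately 163 patients in each group, and 41 patients with normal corticosteroid function who are untreated) are needed". The inflation from 121 per group to that total comes from one further assumption, worded as "Assuming a rate of 75% of corticosteroid insufficiency".

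The same section plans two interim analyses with O'Brien-Fleming alpha spending, "planned respectively after the inclusion of 110 and 220 patients". Allocation is 1:1 (section Randomization). The section Trial status reports 110 patients enrolled by 5 October 2011 and the first interim analysis due in November 2011.

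**The concern.** Both figures describe the number of patients to be randomised in the same trial, and they differ by 50. The article mentions no dropout allowance, non-evaluable fraction, inflation for the interim looks or later increase in sample size that would link them.

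In a fixed-sample trial this would be mainly editorial. Here the maximum also sets the information fraction at each look. An alpha-spending function turns that fraction into the amount of type I error available, so the boundary at the first look depends on which total is meant, and that look was about a month away when the article was written.

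**Working it through.** **Inputs, all from Statistical consideration unless noted:** placebo rate 0.70; treated rate 0.70 − 0.20 = 0.50; two-sided α 0.05; power 0.90; insufficiency rate 0.75; 1:1 allocation (Randomization); looks at 110 and 220; totals 326 (this section) and 376 (abstract).

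**1. Patients with insufficiency per group.** Unpooled two-proportion formula:

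n = (1.960 + 1.282)² × (0.70 × 0.30 + 0.50 × 0.50) / 0.20² = 10.51 × 0.46 / 0.04 = 120.8, rounded up to 121.

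This is the stated figure. The pooled-variance formula gives 124, the arcsine formula 124.1 and the continuity-corrected formula 134.

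**2. Inflation to the number randomised.**

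| Per group | Both groups | Divided by 0.75 |
|---|---|---|
| 121 (stated) | 242 | 322.7 |
| 124 (pooled) | 248 | 330.7 |
| 134 (continuity-corrected) | 268 | 357.3 |

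326 lies between the first two rows. None of these variants reaches 376. Getting from 326 to 376 needs a factor of 376/326 = 1.153, equivalent to an unstated loss of 1 − 326/376 = 13.3%.

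**3. Interim looks as fractions of the maximum.**

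| Maximum | 110/N | 220/N |
|---|---|---|
| 326 | 0.337 | 0.675 |
| 376 | 0.293 | 0.585 |

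The looks are nearly equally spaced for 326 and not for 376.

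**4. Power at each total, at a 75% insufficiency rate.** Patients with insufficiency per group = N × 0.75 / 2.

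| N | Per group | Power, unpooled | Power, pooled |
|---|---|---|---|
| 326 | 122.25 | 90.3% | 89.6% |
| 376 | 141 | 93.8% | 93.3% |

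**5. Effect on the boundaries.** The article names O'Brien-Fleming spending without giving the function. Assuming the Lan-DeMets O'Brien-Fleming-type function, the nominal two-sided levels are:

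| N | First look | Second look | Final |
|---|---|---|---|
| 326 | 0.00074 | 0.0167 | 0.0436 |
| 376 | 0.00029 | 0.0103 | 0.0460 |

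The first-look level differs by a factor of 0.00074/0.00029, about 2.5.

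**6. Effect on type I error.** With classical O'Brien-Fleming bounds for three equally spaced looks (|Z| above 3.472, 2.455 and 2.004), looks at 110, 220 and 326 give 5.0%. The same bounds with one final analysis at 376 give about 5.1%.

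**7. The count of 41.** 163 × 0.25 = 40.75, so 41 is the number per group with normal corticosteroid function. The trial total is 326 × 0.25 = 81.5, about 82.

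**The case against.** The strongest reply is that the operative section is self-consistent. Its inputs, its total and the spacing of its looks all point to 326, so 376 is probably a slip in the abstract. The two sentences are also not strictly exclusive: 326 may be the number needed and 376 a recruitment target with an allowance explained in the full protocol, which a journal article need not reproduce. The CONSORT figure is not available here and could not be checked. Much of this stands, and it is why 326 is the better supported number. It does not remove the need for a correction, because one article gives two totals and does not say how they relate.

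Three stronger readings are tempting, and the documents do not support them.

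- **The power is left open or inadequate.** It is stated as 90% and tied to 121 patients with insufficiency per group. It is met at 326, to within rounding of the formula used, and exceeded at 376.
- **The type I error is materially inflated.** A figure of about 6.5% results if the final bound of 2.004 is applied at 326 and, after a failure there, again at 376. That is a fourth analysis, which the plan neither schedules nor permits. With one final analysis at 376 the error is about 5.1%, and spending boundaries computed at the actual fractions would remove even that drift. A related inference, that the sponsor could choose the closing point after seeing results, is speculation: the trial is double-blind and has an independent DSMB.
- **The 41 is an arithmetic error.** The phrase for each group can govern both counts, and 41 is correct on that reading. The wording is loose; the number is right.

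**Conclusion.** One of the two totals is wrong as written, or lacks the explanation that would reconcile it with the other. On the article's own inputs the supported figure is 326, and the abstract's 376 cannot be derived from them.

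The final analysis point, and therefore the information fractions and the spending boundaries, is ambiguous: 34% and 67% against 29% and 59%. The timing of the looks is not, since they are fixed at 110 and 220 patients. The effects on power and on overall type I error are small. What makes the point worth settling promptly is that the first interim boundary depends on the maximum and the first look was imminent.

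This rests on a 75% insufficiency rate, on patient counts as the measure of information and, for the nominal levels only, on the assumed spending function.

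**What to change.** State one maximum sample size in the abstract and in Statistical consideration, and record it before the first interim result is seen.

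- On the stated inputs it is 326: 163 per group, of whom about 122 have corticosteroid insufficiency and about 41 do not.
- If 376 is the approved figure, give the reason for the additional 50, restate the power as about 93-94% at a 75% insufficiency rate, and compute the spending boundaries at 110/376 and 220/376.
- As a minor clarification, describe the patients with normal corticosteroid function as 41 per group, about 82 in total.

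The cost is a text correction and, if 376 stands, a recalculation of the boundaries. No patients are added beyond the figure already approved.
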